# Funding and insurance

## Budget

Costs related to this research will be covered by the sponsor and include the following:

• Specific insurance

• Data management: eCRFs, data management, statistical analysis

• Time spent for data input

• Variable costs: stationary

## Insurance

The Orleans Regional Hospital has taken out insurance with SHAM for the duration of the study to cover its own civil liability and that of any physicians involved in the trial. It will also insure full compensation for any damages related to the research caused to persons participating in the study and their beneficiaries, unless it can otherwise be proven that it is not liable for the said damages, unless proven against the physician that the damage is not attributable to their fault or that of any intervener, without being able to oppose the fact of a third party or the voluntary withdrawal of the person who had initially consented to participate in the research.

# Practical aspects of the study

The epidemic of COVID-19 has led to a massive influx of patients in hospitals. To date, for the Orléans Regional Hospital, we do not have precise figures for patients meeting the inclusion criteria, but the multicenter aspect will allow us to quickly include the number of patients necessary for statistical analysis.

Patient mobilization is routine in the participating hospital departments. All the centers have medical beds adapted (barriers/tilt of the backrest etc.) to the practice of PP in spontaneously breathing patients.

The medical departments participating in this project have been conducting and participating in research projects for years and the physicians are trained in GCP for research.

For the initiation of the centers and the verification of the data, a CRA is available within the research department of the Orléans Regional Hospital Centre.

Therefore, we have all the operational skills to carry out this study in optimal conditions of safety, ethics and know-how.

# Rules relating to publication

The 2 main authors will be [name] and [name]. The penultimate author will be [name]. The rest of the authorship will depend on the number of inclusions in each center. Communications and scientific reports about the study will be issued under the responsibility of the main investigator and project coordinator with the agreement of the other investigators in charge. The co-authors of the report and publications will be the investigators and clinicians involved, to an extent proportionate to their contribution to the study, and also the associated biostatistician and research scientists.

Publication rules will follow the international guidelines (N Engl J Med, 1997; 336: 309-315).

The trial will be registered on a free access website (ClinicalTrials.gov) before the inclusion of the first patient in the study.

# Appendices

Appendix 1: Illustration of prone positioning (PP) in spontaneously breathing patient

Appendix 2: PP schedule collection

Appendix 3: Example of a follow-up worksheet in the control group

Appendix 4: WHO ordinal scale (according to CAO ; N Eng J Med ; 2020)

APPENDIX 1: Illustration of prone positioning (PP) in spontaneously breathing patient

1. **PUT THE BARRIERS**
2. **KEEP THE CATHETERS AND LINES FREE AROUND THE PATIENT**
3. **ASK THE PATIENT TO LIE ON PRONE POSITION**
4. **NOTE THE START OF PRONE POSITION**
5. **GIVE PATIENT THE CALLBELL for call the staff if necessary**
6. **EXPLAIN TO THE PATIENT THAT THEY MUST LIE 30 min to 1 HOUR PER SESSION (minimum)**

[figure not shown]

APPENDIX 2: PP schedule collection

**Each mobilization (time and duration) during daytime is recorded in a notebook by the patient or by a staff member**

**If you feel tired or your breathing becomes more difficult during your prone position, you can go back to supine. Once you are repositioned, PLEASE NOTE THE TIME OF YOUR RETURN TO SUPINE POSITION.**

| **PP Session n°1** |  |  |  |
| --- | --- | --- | --- |
| Date: | Start time: | End time: | Intolerance: Yes/No  Cause (in plain): |
| **PP Session n°…** |  |  |  |
| Date: | Start time: | End time: | Intolerance: Yes/No  Cause (in plain): |
| **PP Session n°...** |  |  |  |
| Date: | Start time: | End time: | Intolerance: Yes/No  Cause (in plain): |
| **PP Session n°…** |  |  |  |
| Date: | Start time: | End time: | Intolerance: Yes/No  Cause (in plain): |
| **PP Session n°…** |  |  |  |
| Date: | Start time: | End time: | Intolerance: Yes/No  Cause (in plain): |
| **PP Session n°…** |  |  |  |
| Date: | Start time: | End time: | Intolerance: Yes/No  Cause (in plain): |
| **PP Session n°…** |  |  |  |
| Date: | Start time: | End time: | Intolerance: Yes/No  Cause (in plain): |

APPENDIX 3: Example of a follow-up worksheet in the control group

| **Day 1: Date =** | | | |
| --- | --- | --- | --- |
| Chair  Yes/No | Semi-sitting position  Yes/No | Walking around  Yes/No (toilette, transfer alone) | Lateral position: Yes/No |
| **Day 2: Date =** | | | |
| Chair  Yes/No | Semi-sitting position  Yes/No | Walking around  Yes/No (toilette, transfer alone) | Lateral position: Yes/No |
| **Day 3: Date =** | | | |
| Chair  Yes/No | Semi-sitting position  Yes/No | Walking around  Yes/No (toilette, transfer alone) | Lateral position: Yes/No |
| **Day 4: Date =** | | | |
| Chair  Yes/No | Semi-sitting position  Yes/No | Walking around  Yes/No (toilette, transfer alone) | Lateral position: Yes/No |
| **Day 5: Date =** | | | |
| Chair  Yes/No | Semi-sitting position  Yes/No | Walking around  Yes/No (toilette, transfer alone) | Lateral position: Yes/No |
| **Day6: Date =** | | | |
| Chair  Yes/No | Semi-sitting position  Yes/No | Walking around  Yes/No (toilette, transfer alone) | Lateral position: Yes/No |

APPENDIX 4: WHO ordinal scale (according to CAO; N Eng J Med; 2020)

1. Not hospitalized, no limitations of activities
2. Not hospitalized, limitation on activities
3. Hospitalized, not requiring supplemental oxygen
4. Hospitalized, requiring supplemental oxygen
5. Hospitalized, on non-invasive ventilation or high flow oxygen devices
6. Hospitalized, on invasive mechanical ventilation or ECMO or both
7. Death

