## Secondary endpoints

The duration (in days) to improve the clinical WHO ordinal scale from randomization to 28 days between the 2 groups (PP and usual care). This scale is recommended by the WHO (<http://www.who.int/blueprint/priority-diseases/key-action/novel-coronavirus/en/>) and was used in clinical trial of COVID-19 (CAO; N Engl J Med; 2020). This scale is relevant but it could be difficult to use for overloaded wards during an epidemic to exhaustively survey all points. Moreover, because the unit of time is the day, the score is imprecise (e.g., for reasons of feasibility, it is not possible to envisage twice-daily surveying). For this reason, the scientific committee chose not to use this endpoint as primary endpoint.

The rate of endotracheal intubation (%) for invasive mechanical ventilation at 28 days between the 2 groups

The rate of non-invasive ventilation at two pressure levels at 28 days between the 2 groups

The time passed on oxygen therapy from inclusion to day 28 between the 2 groups

The hospital length of stay between the 2 groups

The mortality at 28 days and during the hospital stay between the 2 groups

The rate of transfer to ICU at 28 days

The rate of use of non-invasive ventilation at 2 levels pressure and intubation over the entire hospital stay.

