# Population

## Inclusion criteria

Patients > 18 and < 85 years old

Patients hospitalized with a laboratory-confirmed SARS-CoV-2 infection

Patients on oxygen therapy (nasal cannula, mask or high-flow nasal oxygen therapy)

Patients able to self-position to the prone position or with minimal assistance of one person

Signed the consent form

Patients hospitalized in COVID-19 medical ward for < 72 hr

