## Research duration

Inclusion period: Epidemic COVID-19 period

Duration of intervention: the study intervention will stop when one of the events is reached: initiation of non-invasive or invasive ventilation, death, or patient still hospitalized at day 28 without event. Patients hospitalized for > 28 days will continue to be followed in the study (rate of use of resuscitation, rate of use of non-invasive or invasive ventilation, death).

The duration of participation for each patient corresponds to the hospitalization duration (all wards combined), subject to AEs that would require a longer follow-up.

Total duration of participation in the study for the patient: length of hospitalization

Total duration of the study: 24 months

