## Statistical methods

A detailed analysis plan will be developed prior to the start of the study. The plan will be modified, if necessary, before the statistician is unblinded.

Oatient characteristics will be described by randomization group as number and percentages for categorical variables and mean (standard deviation) or median (25th and 75th percentile) for continuous variables, depending on their distribution.

The main analysis will be conducted on an intention-to-treat basis. However, data for patients withdrawing their consent during the study, in accordance with French law, will not be analyzed.

The primary endpoint (percentage of patients requiring intubation or non-invasive ventilation at 2 pressure levels, or who died within 28 days of inclusion) will be compared between the 2 groups (PP and usual care) by a Mantel-Haenszel 2-test stratified on the stratification variables #2 and #3 (SpO2 and BMI). The effect of the intervention will be expressed in terms of absolute risk difference and its 95% confidence interval (CI). The result of this analysis will be confirmed by a mixed-effect logistic regression analysis, with the recruiting center as the random effect and the study intervention and the stratification variables 2 and 3 as fixed effect variables. Interaction terms between the stratification variables and the intervention will be introduced into the model and retained only if they show a significant effect on the frequency of the outcome. Logistic regression analysis will be used to estimate the odds ratio and its 95% CI.

The binary secondary endpoints (intubation rate, rate of non-invasive ventilation at 2 pressure levels, rate of transfer to ICU, mortality) will be compared between the groups using the same method.

The time to clinical improvement (decrease of 2 points on the WHO scale) will be compared between groups by log rank test and presented as Kaplan-Meier curves. The difference in risk between the groups will be expressed as a hazard ratio (HR) and its 95% CI. This analysis will be secondarily adjusted for stratification variables, and possibly other covariables that would be misbalanced between groups, using a Cox proportional model provided the proportional assumption is verified.

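### Oxygen time is defined up to day 28, but no oxygen data are planned after discharge; the 2-point WHO rule likewise scores a discharge on oxygen as improvement

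*Protocol*

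**What the plan says.** Oxygen time. The Protocol, under Secondary endpoints, lists "The time passed on oxygen therapy from inclusion to day 28 between the 2 groups"; the synopsis and the Secondary objectives give the same window. Section 5.4 (Research duration) states "Total duration of participation in the study for the patient: length of hospitalization", with extension only for adverse events. The last column of the schedule in section 5.3 is hospital discharge or intensive care with mechanical ventilation. Section 5.6 takes everything not listed for the case report form from the hospital record. Section 8.5 plans a day-28 telephone call for patients already discharged, for vital status, and expects no missing data on the endpoint variables.

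WHO scale. All patients enter on oxygen (section 4.1), so they start at level 4, "Hospitalized, requiring supplemental oxygen", or level 5, "Hospitalized, on non-invasive ventilation or high flow oxygen devices". Level 3 is "Hospitalized, not requiring supplemental oxygen". Level 2 is "Not hospitalized, limitation on activities". Section 8.1 reads: "The time to clinical improvement (decrease of 2 points on the WHO scale) will be compared between groups by log rank test". The synopsis objective and the schedule table also use 2 points. The Secondary objectives section and the synopsis endpoint list mention only a decrease in score, and the Secondary endpoints section gives no threshold.

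**The concern.** The oxygen endpoint covers 28 days, but its data collection stops at discharge. A patient sent home on oxygen on day 9 who stops on day 18 has nine further oxygen days inside the window, and no planned procedure records them. Patients already on oxygen at home are excluded at entry, so oxygen after discharge is new, unresolved need of the kind this endpoint should capture.

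The gap matters most if it differs between arms. The trial is open-label (section 5.5), and oxygen indication and weaning are left to the clinicians (section 5.2). More discharges on oxygen in one arm would then look like shorter oxygen therapy in that arm. On the WHO scale the same discharges would count as improvement for patients who started at level 4.

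**Working it through.** **1. The plan's own figure.** The only calculated figure is the sample size for the primary composite. For 4% versus 14%, two-sided 5%, 80% power, pooled variance:

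n per arm = [1.96 × √(2 × 0.09 × 0.91) + 0.8416 × √(0.04 × 0.96 + 0.14 × 0.86)]² / 0.10² = 127.4, so 128; total 256; 256 / 0.98 = 261.2, so 262. This is close to the stated 268. With 134 per arm, power is 82.0% (4% versus 14%) and 86.7% (10% versus 24%). The figure stands, and this point does not touch it.

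**2. Window against data source.**

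| Item | Place in Protocol | Reaches beyond discharge? |
|---|---|---|
| Endpoint window, to day 28 | Secondary endpoints | Yes |
| Participation | 5.4 | No, except for adverse events |
| Schedule of actions | 5.3 | No |
| Source of data not on the form | 5.6, hospital record | No |
| Day-28 call | 8.5 | Yes, but vital status only |

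Section 11.4 mentions a 28-day follow-up but names no oxygen data. For a patient discharged on oxygen before day 28, the endpoint therefore has no planned source for the rest of the window. That does not fit the expectation in section 8.5 of no missing endpoint data.

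**3. What a 2-point decrease means (Appendix 4).**

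- From level 4, levels 2 and 1 qualify. Both are outside hospital and neither mentions oxygen. Level 3, weaned in the ward, is only 1 point lower.
- From level 5, levels 3, 2 and 1 qualify, so weaning in the ward is enough.

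Example: two patients both come off oxygen on day 8 and go home on day 12. The one who started on cannula improves on day 12, the one who started on high-flow on day 8. If any decrease counted, as the Secondary objectives wording allows, 4 to 3 would qualify in the ward, but going home on oxygen (4 to 2) would still count too.

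**4. Possible size, on assumptions only.** Unrecorded oxygen per randomised patient = share discharged on oxygen × further oxygen days before day 28:

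- 5% and 5 days: 0.05 × 5 = 0.25 day
- 20% and 14 days: 0.20 × 14 = 2.8 days
- 10-point difference between arms, 10 days each: 0.10 × 10 = 1 day of spurious mean difference

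These are means, whereas section 8.1 specifies a Mann-Whitney test and a median difference. A simulation on that footing assumed: log-normal oxygen time, median 8 days, log-SD 0.6, capped at 28; 131 per arm (134 × 0.98); patients discharged on oxygen recorded at 40–80% of their true time; no true difference; unstratified test; 4,000 replicates.

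| Share discharged on oxygen, arm 1 / arm 2 | False-positive rate | Spurious median difference |
|---|---|---|
| 0% / 0% | 4.9% | about 0 |
| 10% / 10% | 5.0% | about 0 |
| 20% / 20% | 5.5% | about 0 |
| 30% / 30% | 5.3% | about 0 |
| 10% / 20% | 9.9% | 0.4 day |
| 10% / 30% | 25.4% | 0.7 day |
| 20% / 40% | 24.8% | 0.7 day |

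With a true 25% reduction in oxygen time, power falls from 96.8% (nobody discharged on oxygen) to 95.0% (10% in both arms) and 93.4% (30% in both arms). Equal shares cost little; unequal shares bias the comparison.

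**The case against.** The other side has four good arguments.

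- The written window already runs to day 28, and coding of days after discharge is commonly left to the analysis plan that section 8.1 announces. The first part is right: a reader might infer that discharge ends the oxygen clock or that home days count as zero, but the Protocol says neither. What remains is that an analysis plan can define a rule but cannot recover stop dates that nobody collected. The hospital record may show oxygen at discharge; it is not planned to show when oxygen stopped at home.
- The scale is a published one, taken over unchanged. The Protocol discusses its burden and day-level imprecision and declines to make it primary. This stands: the levels contain no drafting error, and rescoring the scale as the main version would cost comparability with other trials.
- A reader might conclude that both endpoints measure discharge practice rather than respiratory recovery, or that the WHO endpoint merely repeats length of stay. Neither is supported. Patients starting on high-flow can improve in the ward, oxygen time is correct for anyone weaned before discharge, and discharge partly reflects recovery. Time to improvement is a log-rank analysis over 28 days. Length of stay is a Mann-Whitney comparison with no stated limit, and an early death never improves yet may have a short stay.
- Different bars for level 4 and level 5 starters do not by themselves bias a randomised comparison, and no imbalance in discharge on oxygen is shown. Both are correct. The risk is conditional.

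**Conclusion.** The point holds as a mismatch between an endpoint and its data collection. Oxygen time is defined to day 28, no source is planned for it after discharge, and it will be understated for patients discharged on oxygen. Bias between arms requires unequal shares discharged on oxygen. That is possible in an open-label trial with clinician-led weaning, but the documents give no rate, duration or imbalance, so the amount cannot be estimated. The figures under the check are illustrations on assumed inputs.

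On the WHO scale, two narrower statements hold. Under the 2-point rule a level 4 starter can improve only by leaving hospital, with or without oxygen, whereas a level 5 starter can improve in the ward. And the sections that omit the 2-point threshold do not agree with section 8.1. This is a cheap improvement to secondary endpoints.

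**What to change.** 1. Add one discharge field: on oxygen at discharge, yes or no.
2. For those discharged on oxygen, ask the stop date in the day-28 call already planned in section 8.5, and count home oxygen days up to day 28. If this is not feasible, rename the endpoint in-hospital oxygen time in the synopsis, objectives and endpoints.
3. Amend sections 5.4 and 8.5 so that the described follow-up and the missing-data statement match.
4. State the 2-point threshold consistently in the synopsis endpoint list, the Secondary objectives and the Secondary endpoints, in line with section 8.1.
5. Keep the standard 2-point WHO analysis. Add, as supportive, time to first day alive without supplemental oxygen, with patients discharged on oxygen not counted until oxygen stops. This sets the same bar for level 4 and level 5 starters.

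The cost is one field, one question with some recall error in the stop date, and one additional analysis. Only measurement changes; care, the primary endpoint and the sample size do not.
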